## Abstract

**Introduction:**

Approximately 60 000 (9/100) infants are born into water annually in the UK and this is likely to increase. Case reports identified infants with water inhalation or sepsis following birth in water and there is a concern that women giving birth in water may sustain more complex perineal trauma. There have not been studies large enough to show whether waterbirth increases these poor outcomes. The POOL Study (ISRCTN13315580) plans to answer the question about the safety of waterbirths among women who are classified appropriate for midwifery-led intrapartum care.

**Methods and analysis:**

A cohort study with a nested qualitative component. Objectives will be answered using retrospective and prospective data captured in electronic National Health Service (NHS) maternity and neonatal systems. The qualitative component aims to explore factors influencing pool use and waterbirth; data will be gathered via discussion groups, interviews and case studies of maternity units.

**Ethics and dissemination:**

The protocol has been approved by NHS Wales Research Ethics Committee (18/WA/0291) the transfer of identifiable data has been approved by Health Research Authority Confidentiality Advisory Group (18CAG0153).

Study findings and innovative methodology will be disseminated through peer-reviewed journals, conferences and events. Results will be of interest to the general public, clinical and policy stakeholders in the UK and will be disseminated accordingly.

Strengths and limitations of this studyUsing large retrospective and prospective datasets concomitantly provides six years data over a three year study period.Ability to look at all neonatal outcomes and treatments across the wide geographical range and number of units.Using existing, routine data enhanced by prospective data to investigate the safety of waterbirth across a range of outcomes.Data collected will only represent users of Wellbeing Software’s EuroKing maternity software system.Allocation is not random, so unmeasured confounding is possible.

## Introduction

In 1992, the House of Commons Health Committee recommended hospitals should provide women with the use of a birth pool for labour ‘where this is practicable*’*.^1^ In the intervening years, the popularity of the use of water immersion for labour and birth in the UK has increased, and since 2007 The National Institute for Health and Care Excellence (NICE) recommends water immersion analgesia be made available to all clinically appropriate, low-risk women in labour.^2^

The Cochrane review of water immersion during labour provided evidence supportive of pool use for labour analgesia but could not answer the question relating to the safety of waterbirth for mother or baby. The review included 12 trials (3243 women), nine of which focused on the first stage of labour. Results from six studies looking at the first stage of labour found a significant reduction in the rate of regional analgesia/anaesthesia among women allocated to water immersion compared with no immersion (478/1254 vs 529/1245, respectively; risk ratio 0.90; 95% CI 0.82 to 0.99).^3^

Many professionals and parents have strong opinions on waterbirth. Some are great advocates, promoting benefits of waterbirth, while others remain concerned that women who give birth in water may be exposing themselves or their baby to additional unnecessary risks.^4–6^

This study is collecting data on births to all women in 26 UK maternity units from 2015 and is identifying the numbers, proportion and characteristics of women who use water immersion during labour or birth. The study will also establish whether waterbirth is as safe for mothers and their infants as using a pool during labour but getting out prior to birth. Data will be collected on 15 000 waterbirths and 15 000 land births among women with uncomplicated pregnancies from National Health Service (NHS) sites which use Wellbeing Software’s (WS) maternity software system EuroKing. This study will use data recorded routinely as part of standard maternity care and stored on respective NHS site’s servers. For infants admitted to a neonatal unit (NNU), the study will also use data held by the National Neonatal Research Database (NNRD). Data needed to answer some study questions are already recorded, for example, perineal trauma, therefore, data from births from 2015 onwards can be included. Existing, routinely collected data does not capture all information to answer the study questions, data items missing from existing routinely collected data include infants receiving antibiotics without admission to NNU and whether following waterbirth the placenta is delivered in or out of water. Cardiff University (CU) has worked with WS in order to develop study specific data fields which will enable these data to be captured in participating sites from 2019 onwards.

## Methods and analysis

### Primary research objective

To establish whether for low-risk^2^ women who use a pool during labour, waterbirth, compared with leaving a pool prior to birth, is as safe for mothers and infants.

### Secondary objectives

To establish:

Overall proportion and characteristics of women who use a pool for labour or birth, compared with those who do not use a pool.Characteristics of, and outcomes for, women with risk factors, who use a pool during labour.Characteristics of, and outcomes for, women who develop labour complications who use a pool during labour.Factors associated with rates of pool use in individual maternity units.

### Primary outcomes

#### Maternal primary outcome

Obstetric Anal Sphincter Injury (OASIS).

#### Infant primary outcome

A composite of ‘adverse infant outcomes or treatment’ to include:

Any NNU admission requiring respiratory support.Antibiotic administration within 48 hours of birth (with/without culture proven infection).Intrapartum stillbirth or all deaths prior to NNU/postnatal ward discharge.

### Secondary outcomes

#### Maternal secondary outcomes

Maternal intrapartum:

Shoulder dystocia and required management.Management of the third stage of labour (whether the placenta was intended to be, or delivered in or out of water).Obstetric involvement in care.Incidence and management of perineal trauma.Maternal position at birth.

Maternal postnatal:

Duration of postnatal stay.Breastfeeding.Need for higher-level care.Maternal readmission to hospital within 7 days of birth.

### Study design

A natural experiment using a cohort design with a nested qualitative component will answer study objectives using a combination of retrospective and prospective data in electronic NHS maternity and neonatal information systems. The qualitative component will explore factors influencing pool use and waterbirth. CU has partnered with WS who supply EuroKing maternity software system in the UK and the NNRD to link data on infants transferred to NNU.

To answer all objectives approximately 600 000 individual computerised maternity records held on secure NHS servers in 26 NHS sites from January 2015 will be accessed. To provide necessary denominator data and to be able to compare characteristics of pool/non-pool users, a dataset will be extracted relating to women who did not use a pool in labour, a more extensive dataset will be extracted for women who used a pool in labour. An important clinical question is whether there is a differential effect of waterbirth on severe perineal trauma among nulliparous and parous women. A larger sample size is required for the maternal (30 000) compared with the infant (16 200) primary outcome. To inform the maternal primary outcome, severe perineal trauma, which is already collected in the maternity information system at study sites, data will be extracted relating to births between 1 January 2015 to the end of data collection. The infant composite primary outcome includes data items added at site opening, as essential data are not collected routinely. For this reason, data used to inform the infant primary outcome will only include births occurring between the date of an individual site opening and the end of data collection.

NNRD^7 8^ holds individual patient-level data on all infants admitted for NHS neonatal care in England, Wales and Scotland. To obtain detailed treatment and outcome information on infants admitted to NNU, following their mothers’ pool use in labour, the identifiers during the period of prospective data collection will be extracted and matched to any records held by the NNRD.

The primary study aim is to compare maternal and infant outcomes for low-risk women who gave birth in water (group 1) against low-risk women who left the water prior to birth, with no risk-based or clinical reasons (group 2). Figure 1 shows and details the study population groups. Women classified as low risk for study purposes will be at term (37+^0^–41+^6^ weeks gestation), with a singleton fetus in spontaneous labour with an absence of factors that indicate that obstetric or other medical staff should have involvement in her care, or birth in an obstetric unit is advised.^2^

**Figure 1 F1:**
[figure not shown]
Study population groups: overview of the four groups of women within the POOL study population and how these groups will be compared and their data reported. AMU, Alongside Midwifery Unit; FMU, Freestanding Midwifery Unit; OBS, Obstetric Unit; NHS, National Health Service.

### Data providers and datasets

To answer the research questions, two datasets will be used, data extracted from EuroKing maternity software system and data held by the NNRD. EuroKing forms a comprehensive clinical dataset and is currently used by 26 of the maternity NHS Trusts and Health Boards in the UK. All 200 NNUs in England, Wales and Scotland form the UK Neonatal Collaborative and contribute electronic health record data to the NNRD. The NNRD is a national resource formed of the Neonatal Dataset (an NHS Information Standard), comprising of 450 clearly defined variables extracted at patient level from the commercial electronic health record used by all UK NNUs. For the purpose of the POOL study, NNRD data will only be used from England and Wales, as no units in Scotland are supported by WS.

For the retrospective data collection, the data extract will be created by WS for the period January 2015 until prospective data collection commences (site opening). This extract will be created remotely by WS accessing the participating site’s server. A unique study number will be generated prior to data leaving the study sites. WS will transfer a pseudonymised version of this extract to CU and a separate extract of data containing the unique study number, and identifiers to NNRD (pool use) using a secure file transfer process. NNRD will proceed to match the data received from WS to ensure complete records are obtained for infants transferred to NNU and send the pseudonymised dataset to CU.

For prospective data, the same format will be followed as for the retrospective data. Prospective data extracts will include the new variables added to EuroKing (overview of key data items in table 1). A separate syntax will direct the NHS number, unique study number and other identifiers of infants born to all women who used a pool during labour, after site opening, to the NNRD.

**Table 1 T1:** Data sources

**Data provider**	**Data source**	**Data collection period**	**Key data items**
Wellbeing Software	NHS site (Maternity unit)	From January 2015	Routinely collected data items: Demographics (including parity, age, ethnicity and deprivation) Use of pool for labour analgesia/waterbirth Maternal health Labour Birth Pregnancy history Maternal medical and obstetric history Midwifery or obstetric led intrapartum care Delayed cord clamping (>60s after birth) Type of intended care throughout labour Maternal health conditions
Wellbeing Software	NHS Site (Maternity Unit)	From site opening	Risk status at pool entry Reasons for pool exit Obstetric care or input prior to birth Birthing complications Cord snapping prior to clamping Obstetric care in immediate postnatal period. Syntocinon administered in water for labour augmentation Cardiotocography used in water Placenta delivery in or out of water (waterbirths only) Infant antibiotic administration Infant lumbar puncture Infant blood culture Highest neonatal CRP result Treatment for jaundice
National Neonatal Research Database (Data relating to neonates admitted to a neonatal unit)	NHS Site (Neonatal Unit)	From January 2015	Neonatal unit admission and transfer Level of care and number of days received Respiratory support Intravenous antibiotic administration Intrapartum stillbirth or infant death prior to NNU/postnatal ward discharge Timing of cord clamping Apgar scores Resuscitation at birth Culture proven infection Brachial plexus injury Treatment for jaundice Readmission to neonatal unit within 7 days of birth Therapeutic hypothermia
		

CRP, C reactive protein; NHS, National Health Service; NNU, neonatal unit.

NNRD will send three matched datasets to CU for analysis (pilot study, once all sites are opened and at the end of study). Any NNRD data describing infants matched to the study will have NHS numbers removed prior to data being transferred back to CU with the unique study number.

Use of this method of case labelling will enable CU only to hold pseudonymised data, while facilitating the identification of mother/infant dyads and enable the matching of the NNU admission record onto to the mother and infant record held in EuroKing (figure 2).

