### Study participants inclusion and exclusion criteria

Cohort study:

Main analysis: All women at low-risk of complications who use a birth-pool or bath for water immersion during established labour between 1 January 2015 and the end of data collection. Women will be classified as ‘low risk’ if they are at term (37+^0^–41+^6^ weeks gestation), with a singleton assumed cephalic fetus, in spontaneous labour and without pregnancy or intrapartum factors identified by NICE that indicate a need for obstetric or other medical care in labour.

Women who freebirth or give birth prior to arrival at their chosen place of birth or prior to the arrival of a midwife will be excluded.

Descriptive analysis: All women giving birth at a participating NHS site between 2015 and study end.

Eligible sites: NHS maternity services using EuroKing with waterbirth facilities.

Qualitative component phase 1:

(Participants must be from the UK, either within or outside study sites).

Online discussion group participants:

Pregnant women or who have given birth within the last 12 months.Midwives (all grades/positions).Neonatologists, obstetricians and paediatricians (including trainees).

Telephone interview participants:

UK Neonatologists*.Obstetricians*.Paediatricians*.*(including trainees)

Qualitative component phase 2:

Purposively selected case study sites to include midwifery and obstetric units with a range of waterbirth rates (excluding units without a waterbirth facilities).

In each case study site, participants are purposively sampled for discussions, to include the following:

Midwives representing a range of grades and positions.Obstetricians, neonatologists and paediatricians (including trainees).Other unit staff as identified.Women who have given birth in the unit recently.Lay representatives who have experience of supporting local women who have given birth recently—for example, doulas.

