### Main analysis

Primary analysis will compare maternal and infant outcomes only between women without identified pregnancy or intrapartum complications ‘low risk’ who stay and give birth in the pool (waterbirth, group 1) compared with women without identified pregnancy or intrapartum complications ‘low risk’ who use water immersion during their labour but decide to leave the water for birth (out of water, group 2).

The primary analyses are based on a non-inferiority test of birth in water vs on land, comparing (1) the proportion of mothers that have OASIS (based on retrospective and prospective EuroKing data) and (2) the proportion of infants with a composite outcome of ‘adverse infant outcome or treatment’ (based on prospective EuroKing and NNRD data).

To test the primary hypothesis of non-inferiority between birth in water and on land, the maternal and infant primary outcomes will be evaluated for non-inferiority using logistic regression models, in the first instance with no adjustment for covariates. Adjusting for potential confounders may result in a more precise treatment effect estimate. The potential confounders of both primary outcomes (listed in table 2) will be considered. Directed acyclic graphs; visual representations of causal assumptions will be used to identify the presence of confounders.

**Table 2 T2:** Potential confounders for both maternal and infant primary outcomes

	**Maternal outcome: OASIS**	**Adverse infant composite outcome**
Maternal age (years)	X	X
Maternal BMI	X	X
Parity	X	
Duration of labour	X	X
Gestational age at delivery (weeks)	X	X
Birth weight (g)	X	X
Infant head circumference (cms)	X	
Maternal thyroid disease (including hypothyroidism)		X
Prelabour ruptured membranes		X
Intrapartum fever		X
Small for gestational age (weight <10th centile for gestational age)		X
Infant gender		X
Meconium-stained liquor		X

BMI, body mass index; OASIS, Obstetric Anal Sphincter Injury.

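### The OASIS comparator, as the protocol defines it, cannot be identified before site opening, yet the maternal primary analysis pools births from January 2015

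*Protocol article*

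**What the plan says.** In the protocol article, Study design sets the primary comparison as waterbirth (group 1) against "low-risk women who left the water prior to birth, with no risk-based or clinical reasons (group 2". Main analysis describes group 2 in the same sense: low-risk women who choose to get out before birth.

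The maternal primary outcome is "the proportion of mothers that have OASIS (based on retrospective and prospective EuroKing data". For it, Study design states that "data will be extracted relating to births between 1 January 2015 to the end of data collection". The inclusion criteria likewise take low-risk women who used a pool "during established labour between 1 January 2015 and the end of data collection".

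Table 1 (Data providers and datasets) splits the EuroKing items by start date. The row that begins at site opening starts with "Risk status at pool entry Reasons for pool exit Obstetric care or input prior to birth" and goes on to birthing complications. The text before the table says: "Prospective data extracts will include the new variables added to EuroKing". The row available from January 2015 holds general labour, birth, history and care items, including "Maternal medical and obstetric history Midwifery or obstetric led intrapartum care". It lists no reason for leaving the pool.

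The Introduction and Study design justify the use of retrospective births on one ground: perineal trauma is already recorded. Study design limits the infant outcome to births after site opening because essential data items for it are new.

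**The concern.** The test applied to the infant outcome is whether the necessary items were being recorded. For OASIS, the reason given considers only the outcome variable. The variable that separates group 2 from low-risk women who left for clinical need is also new, and Main analysis treats those women as a separate group to be described.

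If the pooled analysis goes ahead as written, the land-birth comparator is defined one way after site opening and necessarily another way before it. Waterbirths do not carry the same contamination, because a woman who had to leave the pool is not in group 1. Suppose residual clinical leavers have more OASIS than women who left by choice. The comparator rate is then too high and waterbirth looks closer to non-inferior than it is. If they have less, the bias runs the other way and power is lost. This is a primary safety outcome with narrow margins (1.0 point for nulliparous and 0.6 points for parous women), so even a small shift in the comparator matters.

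**Working it through.** **1. Reproduce the plan's sample size.** Inputs from Sample size: OASIS 4.6% (nulliparous) and 1.6% (parous), margins 1.0% and 0.6%, true difference zero, one-sided 5%, power 90%.

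n per group = (1.645 + 1.282)² × 2p(1 − p) / margin²

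- Nulliparous: 7517, against 7500 stated.
- Parous: 7491, against 7500 stated.

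The arithmetic is sound. The issue is who enters the comparator.

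**2. Retrospective share.** The strengths list gives six years of data, and Justification of approach puts three of them before site opening. That is 3/6 = 50% of calendar time. It is not a count of births. The Introduction dates the new fields from 2019, which would make the share larger.

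**3. Shift in the comparator rate, nulliparous.**

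Shift = retrospective share × residual share of clinical leavers × (their OASIS rate − 4.6%)

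The residual share and their OASIS rate are assumptions; the documents give neither.

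SE of the risk difference at 4.6% and 7500 per group = √(2 × 0.046 × 0.954 / 7500) = 0.342 points.

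Chance of declaring non-inferiority when waterbirth is truly at the margin = Φ(−1.645 + shift/SE). With no shift it is 5%.

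| Retrospective share | Residual clinical leavers | Their OASIS rate | Shift (points) | False non-inferiority |
|---|---|---|---|---|
| 50% | 5% | 6.5% | 0.05 | 6.6% |
| 50% | 5% | 8% | 0.09 | 8.1% |
| 50% | 20% | 6.5% | 0.19 | 13.8% |
| 50% | 20% | 8% | 0.34 | 25.8% |
| 67% | 40% | 8% | 0.91 | 84.6% |

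The last row puts every input at its extreme.

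**4. Opposite direction.** If the residual clinical leavers had an OASIS rate of 3% (30% share, 50% retrospective), the shift is 0.5 × 0.3 × (3.0 − 4.6) = −0.24 points. Power is then Φ((1.0 − 0.24)/0.342 − 1.645) = 72%, against 90% planned.

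**5. What prospective births alone would support.** Sample size gives 1650 nulliparous waterbirths a year. Assume at least as many eligible land births.

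- Two years: 3300 per group, SE 0.516 points, power Φ(1.0/0.516 − 1.645) = 62%.
- Three years: 4950 per group, SE 0.421 points, power Φ(1.0/0.421 − 1.645) = 77%.
- Reaching 7500 takes 7500/1650 = 4.5 years.
- Parous, three years: 3 × (6600 − 1650) = 14 850 per group, power above 99%.

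The retrospective births are therefore needed to reach the nulliparous target, and dropping them is not free.

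**The case against.** The strongest reply is that exit reason is not the only filter. The inclusion criteria already remove women with pregnancy or intrapartum factors calling for obstetric or other medical care, however they came to leave the pool. Routine items held since 2015 cover labour, birth, history, lead professional and intended care, and many clinical leavers should be visible in them; a caesarean, for example, should be. Table 1 is an overview of key items, Figure 1 is not shown, and this is a condensed article, so a working rule for retrospective births may exist in the full protocol or analysis plan.

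Most of this stands, and it limits the point. A reader might infer that group 2 cannot be identified at all before site opening, or that retrospective group 2 is bound to contain women with operative births. The documents support neither, because a partial proxy is available. Nor do they support taking the 85% figure as the expected error: it stacks extreme assumed inputs and allows nothing for the low-risk criteria or covariate adjustment.

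The mismatch itself survives. No later document can recover an exit reason that was not recorded; it can only supply a proxy, and a proxy is a different comparator from the one defined here. Adjustment for the Table 2 covariates does not settle it either, since exit reason is not among them.

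**Conclusion.** The concern holds in a limited form. The definition of group 2, the start date of the items that establish it and the birth period of the maternal analysis do not fit together. For about half the calendar time, the OASIS comparator can only be approximated.

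The consequence may be modest or material. With routine filters that leave a 5% residual share, false non-inferiority is about 7–8% instead of 5%. With a 20% share at 6.5% it is about 14%, and larger shares give more. These figures rest on an assumed residual share and OASIS rate, on half the data being retrospective by calendar time, and on the plan's 4.6% and 7500 per group. The direction is also assumed: a lower OASIS rate in the residual women would cost power instead. A reader might infer that the documents show a bias in favour of waterbirth. They show only that the comparator differs between eras and that the resulting bias has not been bounded.

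**What to change.** 1. Assign both groups in the pooled OASIS analysis by one stated rule that uses only items recorded since January 2015. Apply it identically to waterbirths and land births, before and after site opening. Candidate elements are spontaneous vaginal birth, midwifery-led care up to birth and no coded intrapartum complication.
2. In the prospective births, report how often that rule misclassifies women against the recorded exit reason.
3. Prespecify a prospective-only OASIS analysis using recorded exit reasons as a required sensitivity analysis. Judge it on consistency of the estimate with the pooled result. It should not be a gate on the non-inferiority claim, because its nulliparous power is below the planned 90%.
4. State that power: about 77% at three prospective years (4950 per group), or about 62% at two (3300 per group).

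The cost is plan wording and extra analysis of data already due to be extracted. The downside is a supporting nulliparous analysis with less than 90% power, which may be inconclusive on its own.
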